### Proposed sample size and power calculation

In two small studies that examined the efficacy of rTMS in the treatment of borderline personality disorder, medium to large effect sizes were demonstrated (Cohen’s d = 0.74–2.79, [18, 61]). Since these pilot studies had small sample sizes, the possibility of an alpha error and an overestimation of the effect size cannot be ruled out. In order to use a conservative estimate, Whitehead et al. [62] recommend a group size of N = 15 for pilot studies if mean effect sizes are to be expected in the outcome parameter. Since we conduct a pilot study with an inter-subject design with two groups and allow for a 25% contingency for dropouts, we will include N = 53 participants in the study totally for both interventions. Based on a power/sample size calculation with G-POWER [63], the resulting total sample size of 40 patients is sufficient to detect a small to medium effect (f = 0.2) with alpha = 0.05 and a power (1-beta) of 80% (for testing the interaction in a repeated measurement design with two groups). Thus, with the projected sample size a clinical relevant effect of rTMS (in addition to DBT) can be revealed with sufficient power.

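### 40 patients cannot give 80% power for a small-to-medium group-by-time effect: on G*Power's default scale f = 0.2 is a 0.8 SD difference in BSL-23 change, and on the scale where it is d = 0.4 the power is 22–23%

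*Protocol article*

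**What the plan says.** The section on proposed sample size and power calculation cites two small rTMS studies in borderline personality disorder with Cohen's d of 0.74 to 2.79, which it calls medium to large. It warns that "the possibility of an alpha error and an overestimation of the effect size cannot be ruled out". It then cites a pilot-study recommendation of 15 per group, allows 25% for dropout and arrives at 53 enrolled.

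The power statement follows. Citing G*Power, it says that a total of 40 patients "is sufficient to detect a small to medium effect", which it gives as f = 0.2. The significance level is 0.05, the power is 80%, and the test meant is the group-by-time interaction with two groups. The section then draws the conclusion that "with the projected sample size a clinical relevant effect of rTMS (in addition to DBT) can be revealed with sufficient power".

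Two other sections fix what is tested. Primary outcome measures defines the endpoint as the between-group difference in BSL-23 change from T0 to T1. Data analysis describes a two-group, T0 versus T1 design, analysed with a mixed model over all assessed time points, with the interaction tested at p ≤ 0.05.

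**The concern.** Calling f = 0.2 small to medium follows the convention for a one-way comparison of two groups, where d = 2f = 0.4. In G*Power's default set-up for a within-between interaction, f measures the interaction effect in the cells of the design. The between-arm difference in change that it implies is twice as large as the one-way reading suggests.

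The Discussion says the results will inform whether and how later studies should pursue iTBS as an add-on. A reader told that the trial had 80% power for a modest effect could take a non-significant interaction as evidence that no such effect exists. If the true difference were 0.4 to 0.5 SD, a non-significant result would be the more likely outcome at most plausible correlations.

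**Working it through.** **Inputs from the article.** f = 0.2, alpha 0.05, power 80%, N = 40 in total, two groups, 1:1 allocation, interaction test, G*Power. The T0–T1 correlation (rho), the number of measurements m and the G*Power effect-size option are not stated, so they are treated as assumptions and varied.

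**1. Reproducing N = 40.** Under G*Power's default option, lambda = f² · N · m / (1 − rho), with df1 = m − 1 and df2 = (N − 2)(m − 1). For m = 2 and rho = 0.5, lambda = 0.04 · 40 · 2 / 0.5 = 6.4 on F(1, 38).

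| Setting (default option) | Power at N = 40 | N for 80% |
|---|---|---|
| m = 2, rho 0.5 | 69.3% | 52 |
| m = 2, rho 0.60 | 78.7% | 42 |
| m = 2, rho 0.61 | 79.7% | 42 |
| m = 2, rho 0.62 | 80.7% | 40 |
| m = 3, rho 0.5 | 78.2% | 42 |
| m = 5, rho 0.5 | 90.2% | 32 |

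The stated inputs do not fix N. A correlation of about 0.61 with T0 and T1 gives the published figure to within rounding. Enrolment also agrees: 53 · 0.75 = 39.75.

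**2. What f = 0.2 means under the default option.** With two groups and two times, the interaction cell effects are +0.2, −0.2, −0.2 and +0.2 SD. The difference in change is (0.2 + 0.2) − (−0.2 − 0.2) = 0.8 SD.

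The noncentrality confirms this. A two-sample test of change scores has lambda = N · D² / (8(1 − rho)), where D is in SDs of BSL-23 at one time point. Setting f² · N · 2 / (1 − rho) equal to it gives D² = 16f², so D = 4f = 0.8. The correlation cancels. At N = 40 and rho = 0.5 both routes give lambda 6.4 and 69.3% power.

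In SDs of the change score, this difference is 0.8 / √(2(1 − rho)): 0.68 at rho 0.3, 0.80 at 0.5, 0.91 at 0.61 and 1.03 at 0.7.

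**3. More than two time points.** Table 1 of the article schedules BSL-23 five times. With m = 3 to 5, f = 0.2 has no single equivalent. Over the monotone patterns tried, the smallest T0–T1 difference is 0.80 to 0.85 SD. At m = 5 an immediate step gives 1.0 SD and a linear divergence 1.13 SD.

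**4. The other G*Power options.** As in Cohen: lambda = f² · N = 0.04 · 40 = 1.6. As in SPSS: lambda = f² · (N − 2) = 0.04 · 38 = 1.52. Here f = 0.2 is about d = 0.4 in change, so the label fits. Power on F(1, 38) is 23.4% and 22.5%, and 80% power needs 200 and 202 patients.

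**5. Power at N = 40 for a small-to-medium difference in change** (change-score test, m = 2, D in single-time-point SDs):

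| True difference | rho 0.3 | rho 0.5 | rho 0.61 | rho 0.7 |
|---|---|---|---|---|
| 0.4 SD | 18% | 23% | 29% | 36% |
| 0.5 SD | 26% | 34% | 41% | 51% |

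As an example, 0.4 SD at rho 0.61 gives lambda = 40 · 0.16 / (8 · 0.39) = 2.05. Power for 0.4 SD comes close to 80% (79%) only near rho = 0.9. Baseline adjustment helps modestly: 30% at rho 0.5 and 41% at rho 0.7 for 0.4 SD.

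**6. Precision at N = 40.** The 95% CI half-width is t(38) · √(2(1 − rho) · 4/40), with t(38) = 2.024. This is 0.64 SD at rho 0.5 and 0.57 SD at rho 0.61.

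**The case against.** The strongest defence is that the settings are not visible. The 0.8 SD equivalence is exact only for the default option with two measurements, and the article states neither. Under another option the label would be right. This stands as a limit on the mechanism. It does not rescue the sentence, because the options that make the label right reduce power to 22–23%.

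Four stronger readings are tempting, and the document does not support them:

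- **That N = 40 is a miscalculation.** An unstated correlation of about 0.61 reproduces it.
- **That the plan presents f = 0.2 as conservative.** In the article that description introduces the pilot recommendation of 15 per group. The plan exceeds that recommendation, with about 20 per group analysed.
- **That 0.8 SD already lies inside the published d range, which may be inflated.** The article does not say whether d = 0.74 to 2.79 is between-arm or pre-post, or which SD it uses, so the two figures may not share a scale.
- **That a null result would wrongly stop the confirmatory trial.** The Discussion calls the study exploratory and promises feasibility and effect-size measures. No rule ties the next trial to a p-value.

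It is also fair that low power is acceptable in a pilot, and that the article sets no threshold for clinical relevance, so a 0.8 SD difference cannot be said to fall outside it. The objection to the concluding sentence is therefore that it is unqualified.

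**Conclusion.** The point holds. No reading tried makes both the small-to-medium label and 80% power true. Either the detectable difference in BSL-23 change is about 0.8 SD, with 80% power resting on a T0–T1 correlation near 0.61, or the effect is about d = 0.4 and power is 22–23%. At that same correlation of 0.61, the chance of detecting a difference of 0.4 or 0.5 SD is 29% or 41%.

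The error lies in the effect label and in the unqualified sufficient-power conclusion, not in the number of patients. The size of the shortfall depends on the correlation, which the article does not give; the range 0.3 to 0.7 is shown for that reason. The conclusion that the two claims conflict does not depend on it within that range.

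**What to change.** 1. State the G*Power effect-size option, the number of measurements and the correlation used.
2. Replace the small-to-medium label for f = 0.2 with the between-arm difference in BSL-23 change that it represents: 0.8 SD of BSL-23 at a single time point, a large effect, if the default option with T0 and T1 was used.
3. Give power for differences of 0.4 and 0.5 SD at that same correlation, so that these figures and the stated 80% rest on one set of assumptions. At 0.61 they are 29% and 41%. At 0.5 they are 23% and 34%, and the 80% itself becomes 69%.
4. Limit the sufficient-power sentence to effects of about 0.8 SD.
5. In keeping with the pilot aim, say that the result will be interpreted through the estimate and its 95% CI (about ±0.57 SD at correlation 0.61, ±0.64 SD at 0.5), and that a non-significant interaction will not be read as absence of effect.

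This changes wording and reported figures only, with no extra patients and no change to the design. The one drawback is a less favourable power statement.

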### Data analysis

Regarding therapy response, a 2 × 2-factorial between-subjects design with the between-subject factor stimulation (TMS vs. Sham) and the within-subject factor time (T0 vs. T1) will be conducted. To deal with a possible bias by treatment drop-out, a Linear Mixed Repeated Measure Model approach will be applied considering all assessed timepoints and the primary outcome (differences in BSL-23 reduction over time between study groups, i.e. interaction time*group) will be tested for significance (p ≤ 0.05). In case of relevant pre-treatment differences, these will be included in the model as covariates to adjust for. Likewise, secondary outcomes will analyzed accordingly.

In a second step, patients will be grouped into responder and non-responder. Group assignment will be performed post-hoc and based on the Reliable Change Index (RCI) as suggested by Jacobson and Truax [64]. An RCI above the 95% confidence limits (+/= 1.96) indicates a reliable change (p < 0.05). To identify parameters which are relevant for therapy response, group comparisons will be performed on secondary outcome variables of T0, using MANOVA models with the independent factor therapy response (responder vs. non-responder) and secondary outcome variables of T0 as dependent variables. Analyses will be corrected for multiple comparisons using Bonferroni Correction and partial eta-square will be determined to report effect size.

Analyses will be conducted with IBM SPSS [65].

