### Assessments

After successful study enrollment, before commencement of the stimulation, the following target parameters are recorded at baseline (see Table 1).

**Table 1 Tab1:** Assessment schedule throughout the study

Time	Screen-ing		Baseline	Treatment phase																				Post-intervention examination
Week				1					2					3					4					
Visit	T0			V1	V2	V3	V4	V5	V 8	V9	V10	V11	V 12	V 15	V 16	V 17	V 18	V 19	V22	V23	V24	V25	V26	T1
Day			− 3	1	2	3	4	5	8	9	10	11	12	15	16	17	18	19	22	23	24	25	26	26
MRI	X																							
Consent/information/data protection	X																							
Inclusion/exclusion criteria	X																							
SKID V PD	X																							
Mini-DIPS-OA	X																							
Psychiatric history	X																							
Medical history	X																							
Physical examination	X																							
Neurological Examination	X																							
MADRS	X												X											X
Pregnancy test	X																							
BSL-23			X					X					X					X						X
GAF			X																					X
BIS-15			X																					X
BDI-II			X					X					X					X						X
SCS-D			X																					X
Default motor threshold				X										X										

*Note*. T0 = baseline, V1–V26 = treatment phase, T1 = post-treatment

Short version of Borderline Symptom List (BSL-23) [42], second edition of Beck’s Depression Inventory (BDI-II) [43], Global Assessment of Functioning Scale (GAF) [44] and the Baratt Impulsiveness Scale, short form (BIS-15) [45]. Further, the German short version of the Self Compassion Scale (SCS-D) [46], the Montgomery–Åsberg Depression Rating Scale (MADRS) [47] and a Delay Discounting task [48] will be used (see detailed description below).

At the end of each week with iTBS/sham intervention, patients are asked to complete a BSL-23 and BDI-II questionnaire to assess symptom severity. Possible undesirable side effects of the stimulation are assessed and recorded by the practitioner after each treatment according to routine trial (serious) adverse events monitoring. At the end of the intervention period (after four weeks), further assessments are made for MADRS, GAF, BIS-15, SCS-D. Moreover, to check for a potential experimenter bias, participants’ belief about whether they took part in the verum or sham treatment condition are assessed after the first iTBS session and at post-intervention.

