### Primary outcome measures

Primary outcome is the difference of improvement of borderline symptomatology between the two groups quantified by changes in the short version of the BSL-23 [42, 49] from baseline (T0) to post intervention (T1). The BSL-23 is a validated self-rating measure of borderline personality disorder symptoms. It contains 23 items that are scored from 0 = not at all to 4 = very strong. All items concern the last week, e.g. ‘In the course of last week, I felt helpless’ or ‘In the course of last week I was afraid of losing control’. The BSL-23 has shown good convergent validity, *r* = 0.89 [49] and reliability, *α* = 0.94–0.96 [42].

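### The plan states conflicting primary tests: a two-level T0/T1 comparison, and a time-by-group interaction in a model over all BSL-23 assessments with no T1 contrast named

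*Protocol article*

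**What the plan says.** Under Primary outcome measures, the outcome is the between-group difference in improvement, measured by "changes in the short version of the BSL-23 [42, 49] from baseline (T0) to post intervention (T1"). That is a single comparison of two changes.

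Data analysis begins with a 2 × 2 layout and "the within-subject factor time (T0 vs. T1) will be conducted". The Abstract describes time in the same way. The next sentence, giving drop-out as the reason, says that "a Linear Mixed Repeated Measure Model approach will be applied considering all assessed timepoints". That same sentence identifies the primary outcome as "differences in BSL-23 reduction over time between study groups, i.e. interaction time*group" and tests it at the 5% level.

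Under Assessments, Table 1 lists BSL-23 at five occasions: baseline (day −3), V5, V12, V19 and T1. The text agrees: "At the end of each week with iTBS/sham intervention, patients are asked to complete a BSL-23 and BDI-II questionnaire".

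Proposed sample size and power calculation claims 80% power with 40 patients at f = 0.2 for an interaction in a two-group repeated-measures design. It gives neither the number of measurements nor their correlation.

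**The concern.** A time factor with two levels cannot hold five assessments, so the two consecutive sentences in Data analysis do not describe the same test. With T0 and T1 only, the interaction is exactly the declared outcome. With all five occasions, it is something else:

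- **Time categorical:** a 4-df omnibus test of any difference in profile shape, with no direction and no specific link to T1.
- **Time linear:** a comparison of slopes across the whole period.

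The tests can disagree on the same data. A between-arm difference that appears during treatment and has gone by T1 could be declared a positive primary result. A real T1 difference could be missed by one test and found by another. If the choice is still open when results are seen, the 5% level no longer belongs to one pre-specified test.

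**Working it through.** **Inputs from the article.** 40 evaluable patients with 1:1 allocation, hence 20 per arm; five BSL-23 occasions; α = 0.05; f = 0.2.

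**Assumed, because the article gives neither.** SD 1 at each occasion, compound symmetry with correlation ρ = 0.5, and two between-arm difference profiles d over the five occasions:
- transient: 0, 0.8, 0.8, 0.4, 0 SD (no difference at T1)
- linear build-up: 0, 0.2, 0.4, 0.6, 0.8 SD

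**Step 1. The plan's own power figure.** For a within-between interaction with m measurements, λ = f²·N·m/(1 − ρ), with df (m − 1) and 38(m − 1).
- m = 2, ρ = 0.5: λ = 0.04 × 40 × 2/0.5 = 6.4; power 69%.
- m = 5, ρ = 0.5: λ = 0.04 × 40 × 5/0.5 = 16; power 90%.
- 80% is reached with m = 2 at ρ of about 0.61, and with m = 5 at ρ of about 0.35.

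The stated 80% can therefore be neither confirmed nor refuted, and it does not show which test was meant.

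**Step 2. Categorical time, 4-df interaction.** λ = (N/4)·Σ(d − mean d)²/(1 − ρ), df 4 and 152.
- Transient: mean 0.4, sum of squares 4 × 0.16 = 0.64, λ = 10 × 0.64/0.5 = 12.8; rejection 82%.
- Linear: mean 0.4, sum of squares 0.16 + 0.04 + 0 + 0.04 + 0.16 = 0.40, λ = 10 × 0.40/0.5 = 8.0; power 59%.

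**Step 3. Linear time, slope by group.** Weights w = −2, −1, 0, 1, 2 (Σw² = 10). Variance of the between-arm difference in the weighted score = 10(1 − ρ) × 2/20 = 0.5.
- Transient: Σwd = −0.8 + 0.4 = −0.4, λ = 0.16/0.5 = 0.32; rejection 9%.
- Linear: Σwd = −0.2 + 0.6 + 1.6 = 2.0, λ = 4/0.5 = 8.0; power 80% with 152 error df (79% with 38).

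**Step 4. The declared outcome, 1-df T0-to-T1 contrast.** Variance of the between-arm difference in change = 2(1 − ρ) × 2/20 = 0.1, df 38.
- Transient: difference 0; rejection 5%.
- Linear: λ = 0.64/0.1 = 6.4; power 69%.

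| Test | Transient (no T1 difference) | Linear to 0.8 SD |
|---|---|---|
| 4-df interaction | 82% | 59% |
| Slope by group | 9% | 80% |
| T0-to-T1 contrast | 5% | 69% |

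**Step 5. Sensitivity to ρ.** At ρ = 0.3 and 0.7, the 4-df test rejects in 66% and 97% of trials for the transient profile. For the linear profile it has 44% and 83%, against 55% and 89% for the contrast. A simulation of 20,000 trials per scenario gave 54% for the linear profile at ρ = 0.5 with an unstructured covariance, so the pattern does not rest on compound symmetry alone.

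**The case against.** The article never says that time has five levels or that the test is an omnibus one. It twice describes time as T0 against T1, the outcome is T0-to-T1 change, and the stated reason for using every assessment is drop-out. On a charitable reading, the interim visits only support estimation while the target stays at T1. A condensed article may also leave time coding to a fuller document. And the illustrative profile is invented: a 0.8 SD benefit that vanishes while daily stimulation continues.

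Much of this stands. A reader might infer that the plan has fixed a 4-df test as its primary analysis. The text does not support that, since the two-level and slope readings are also open. Nor can one say in general that the planned interaction loses power. Under linear growth a slope test beats the contrast (80% against 69%), and for an early, sustained 0.8 SD effect even the 4-df test is level with it (71% against 69%). It would also be wrong to say that the stated power fits neither model, because suitable correlations make it fit either.

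What does not stand is that this is merely detail left to another document. The article names the effect, the data and the threshold for its primary test, and these conflict with its own definitions of the time factor and the outcome.

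**Conclusion.** The concern holds as an internal contradiction over which test is primary. That part follows from the text and Table 1 and needs no assumption. The percentages are illustrations: they depend on how time is coded, on the assumed profiles and on the assumed correlation. They show that the candidate tests can give opposite answers, with 82%, 9% and 5% rejection when the T1 difference is zero. They are not estimates of this trial's error rate.

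Severity is moderate. The Discussion presents the study as an exploratory pilot that should supply effect sizes for a later confirmatory trial, so no efficacy decision rests on this p-value alone. That aim does, however, need an estimated T1 difference with its uncertainty, which an omnibus F test does not provide.

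**What to change.** In Data analysis:
- Keep all five BSL-23 assessments in the mixed model, with time as a factor. This preserves the drop-out rationale.
- Declare the between-arm contrast in T0-to-T1 BSL-23 change (1 df) as the single primary test, two-sided 5%, reported with its estimate and 95% CI.
- Report the omnibus interaction and the weekly profiles as descriptive.
- Correct the 2 × 2 between-subjects label: stimulation is between subjects, time is within subjects, and the fitted model has five occasions. Align the Abstract.

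In Proposed sample size and power calculation, state the number of measurements and the correlation that were used.

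The cost is a few sentences, with no new data or software. There is a small statistical price: under some effect shapes the contrast has less power than a slope or omnibus test, for example 69% against 80% for the slope test under linear growth. The change should be made before anyone sees results by arm.

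### Adjusting only for observed baseline differences neither corrects chance imbalance nor gains precision in the time-by-group test; baseline BSL-23 adjustment should be pre-specified

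*Protocol article*

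**What the plan says.** Under Data analysis, the article sets a design with stimulation group as the between-subject factor and time (T0, T1) as the within-subject factor. It then applies a linear mixed repeated-measures model to all assessed time points and tests the BSL-23 time-by-group interaction at p ≤ 0.05. T0 is therefore an outcome value, not a covariate. On adjustment it says only: "In case of relevant pre-treatment differences, these will be included in the model as covariates to adjust for". It does not say what makes a difference relevant, which variables qualify, or whether a covariate enters alone or with time. Secondary outcomes follow the same approach.

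The baseline needed for adjustment exists: under Assessments, "before commencement of the stimulation, the following target parameters are recorded at baseline". Table 1 lists BSL-23 at baseline, at the end of weeks 1 to 3, and at T1, five assessments in all. No planned adjustment for baseline BSL-23 appears anywhere.

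The sample-size section calls "the resulting total sample size of 40 patients" "sufficient to detect a small to medium effect (f = 0.2") "with alpha = 0.05 and a power (1-beta) of 80"%, the test being described as "for testing the interaction in a repeated measurement design with two groups".

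**The concern.** Allocation is randomised 1:1, so any baseline difference between arms is chance. A rule that waits for such a difference makes the primary model depend on the data. More important, it does not do what it is meant to do. When T0 is an outcome row, a covariate that shifts all of a patient's values equally drops out of that patient's change, and so out of the interaction.

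What is at stake is precision and regression to the mean. An unadjusted comparison of change leaves part of any chance BSL-23 imbalance in the estimated effect. It also has a larger variance than a comparison that conditions on baseline. The Discussion says the study's effect sizes will inform a confirmatory trial, so both matter even in a pilot.

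**Working it through.** **Inputs.** From the article: f = 0.2, alpha 0.05, power 80%, 40 evaluable patients (20 per arm), two groups, T0 and T1. Assumption: the correlation ρ between repeated BSL-23 scores is not stated, so a range of 0.3 to 0.8 is shown, with equal SDs at both times.

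**The plan's own figure.** In the G*Power convention for a within-between interaction, λ = f²·N·m/(1−ρ) with df 1 and N−2 when m = 2.
- At ρ = 0.5: λ = 0.04 × 40 × 2/0.5 = 6.4, power 69%; 80% would need N = 52.
- N = 40 gives 80% with two time points only if ρ is about 0.61. Without a stated ρ, the 40 can be neither confirmed nor refuted.
- Dropout: 40/0.75 = 53.3, in line with the 53 to be enrolled.

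**Effect in SD units.** In a 2 × 2 layout f = 0.2 means a between-group difference in change of 4f = 0.8 SD. Check: 0.8²/[2(1−0.5) × 4/40] = 0.64/0.1 = 6.4, the same λ.

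**Does a covariate move the interaction?** Random-intercept mixed models were fitted to single simulated data sets of 40 patients:

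| Data | Covariate (main effect) | Interaction | SE |
|---|---|---|---|
| 2 times, complete | none | −0.557 | 0.215 |
| | another baseline variable | −0.557 | 0.215 |
| | baseline of the outcome | −0.557 | 0.209 |
| 5 times, complete | none | −0.812 | 0.274 |
| | another baseline variable | −0.812 | 0.274 |
| | baseline of the outcome | −0.812 | 0.274 |
| 5 times, 25% dropout | none | −0.945 | 0.335 |
| | another baseline variable | −0.937 | 0.335 |
| | baseline of the outcome | −0.872 | 0.325 |

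In complete data the estimate never moves. With dropout it moves little: by 0.007 for another variable, and by 0.073 (about a fifth of the SE) for the outcome's own baseline. A covariate-by-time term does change it (two times: −0.560, SE 0.218).

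**Regression to the mean.** Given a chance baseline difference δ, the expected difference in change is the true effect minus (1−ρ)δ. With 20 per arm, the SE of δ is √(2/20) = 0.316 SD. At ρ = 0.5 a one-SE imbalance shifts the estimate by 0.5 × 0.316 = 0.158 SD, about 20% of 0.8 SD.

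**Precision.** The variance of change is 2(1−ρ); the residual variance of T1 given T0 is 1−ρ². The ratio is (1−ρ²)/[2(1−ρ)] = (1+ρ)/2. Adjusted power uses λ = 0.64/[(1−ρ²) × 4/40], divided by 1 + 1/36 as an allowance for chance imbalance, with df 1 and 37. At ρ = 0.5: 0.64/0.075 = 8.53, then 8.53/1.028 = 8.30.

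| ρ | Variance ratio | Power, change | Power, adjusted |
|---|---|---|---|
| 0.3 | 0.65 | 55% | 72% |
| 0.5 | 0.75 | 69% | 80% |
| 0.61 | 0.81 | 80% | 87% |
| 0.7 | 0.85 | 89% | 93% |
| 0.8 | 0.90 | 97% | 98% |

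**The conditional rule.** It was simulated as: use analysis of covariance if baseline BSL-23 differs at p < 0.05, otherwise compare change. It triggered in about 5% of trials. Power was 69% at ρ = 0.5 and 81% at 0.61, essentially that of change alone. Type I error was 3.9% and 4.7%.

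**Five visits.** Assume compound symmetry, ρ = 0.5 and a linear build-up (0, 0.2, 0.4, 0.6, 0.8 SD).
- Unadjusted: the squared deviations of these differences from their mean sum to 0.4, so λ = (40/4) × 0.4/0.5 = 8.
- With a common baseline mean: λ = (40/4) × [1.2 − (0.5/3) × 2²]/0.5 = 10.67, where 1.2 is the sum of squares and 2 the sum of the differences.
- Power rises from 59% to 73% for the 4-df interaction and from 80% to 90% for a linear-slope interaction.

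**The case against.** The strongest objection is that two possible complaints undercut each other. If a main-effect covariate cannot move the interaction, then choosing it after seeing the data cannot steer the primary result. That stands. Analyst discretion matters materially only if covariates enter with time, and then the invariance no longer applies. The article also says the analyses will be blinded to allocation, which limits directional choice. A reader might still infer that the rule inflates type I error; the simulated rule did not. Entering baseline BSL-23 in every trial while T0 remains an outcome row, with the random-intercept variance at zero, gave 5.8% to 7.2% in simulation. But the article neither names BSL-23 as a covariate nor enters it always, so this does not describe the stated rule.

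A reader might also infer that the rule can never alter the test. The article does not say that covariates enter as main effects only, and it expects dropout, so the invariance needs both qualifications.

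The two-point power figures are not the power of the five-visit model the article describes. That is correct. It changes the size of the gain but not its existence, as the five-visit calculation shows.

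Six scales have a pre-stimulation score, so one could compute 1 − 0.95⁶ = 26% as the chance that some covariate is triggered. That needs independent scales and a p < 0.05 trigger. The article gives no trigger, and BDI-II and MADRS both measure depression, so no weight is placed on it.

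Finally, this is a pilot, and an analysis plan not shown may define relevance. But the conditional rule is stated in this document, and the same document claims sufficient power.

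**Conclusion.** The point holds in a limited form. The stated rule is data-driven. For main-effect covariates in complete data it leaves the time-by-group estimate unchanged, and nearly so with dropout. It therefore neither corrects chance imbalance nor recovers precision, unless a time interaction is added that the text does not state. The consequence is lost precision and uncorrected regression to the mean, not a demonstrated type I error problem.

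The size depends on the unstated ρ: for the T0-to-T1 contrast with 40 patients and 0.8 SD, about 17 points of power at 0.3, 11 at 0.5, 7 at 0.61 (where the plan's own 80% is met) and 1 at 0.8. A reader might call this gain free; it needs no more patients or data, but it uses about one degree of freedom and changes the form of the primary model. It should be changed, but it does not invalidate the trial.

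**What to change.** Delete the conditional rule and pre-specify adjustment for baseline BSL-23 in one of two forms:

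- keep all five visits as outcomes, constrain the arms to a common baseline mean, and make the treatment contrast at T1 the primary test; or
- use the post-baseline visits as outcomes, with baseline BSL-23 and its interaction with visit as covariates.

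Simply adding baseline BSL-23 to the present model, with T0 still an outcome row, is not a substitute: it leaves the complete-data estimate where it was. Treat each secondary scale in the same way, with its own baseline. Align the test named in the sample-size section with the chosen form, and state the assumed ρ there.

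The cost is a reworded primary model and about one degree of freedom. The baseline scores are already scheduled, so no extra patients, visits or data are needed.
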